## Abstract

**Background:**

India is undergoing a demographic transition characterized by population aging and is witnessing a high dementia rate. Although nearly 7 million people live with dementia in India, dementia awareness is poor, and current resources addressing dementia care are basic and often incomplete, duplicated, or conflicting. To address this gap, this study aims to use digital media, which has had a massive technological uptake in India, to improve dementia care in India.

**Objective:**

The objective of this paper is to describe an intervention study design that examines the feasibility and acceptability of Moving Pictures India, a digital media resource to improve dementia care in India.

**Methods:**

This study employs a mixed methods design and is divided into 4 phases: (1) video interviews with Indian caregivers and health professionals; (2) coproduction of resources; (3) pilot randomized controlled trial (RCT); and (4) dissemination and analytics. The pilot RCT will follow an experimental parallel group design with 2 arms aiming to assess the impact, feasibility, and acceptability of the developed resources. The primary outcome measures for the pilot RCT will be feasibility and acceptability, while the secondary outcome measures will be caregiver burden, mood, and quality of life.

**Results:**

This study received funding from the Alzheimer’s Association in the United States in July 2021. In 2023, we will enroll 60 dementia caregivers (40 caregivers in the intervention arm and 20 in the control) for the pilot RCT. The study has been approved by the National Institute of Mental Health and Neuro Sciences Ethics Committee (26th IEC (BEH.SC.DIV.)/2020-21 dated November 11, 2020); the Health Ministry's Screening Committee, India (proposal ID 2020-10137); the Curtin University Human Research Ethics Committee (approval number HRE2020-0735); and the NARI Research Governance Office (site-specific approval dated March 17, 2021).

**Conclusions:**

This protocol is designed to deliver unique, coproduced, and evidence-based media resources to support caregivers of persons with dementia in India and other countries aiming to utilize digital media for dementia care. If the intervention is found feasible and acceptable, postpiloting analytics and qualitative feedback will be used to develop an implementation trial to evaluate the effectiveness of the potential low-risk high-benefit intervention in practice.

**Trial Registration:**

Clinical Trials Registry-India CTRI/2021/01/030403; http://ctri.nic.in/Clinicaltrials/pmaindet2.php?trialid=50794

**International Registered Report Identifier (IRRID):**

DERR1-10.2196/38456

## Introduction

India, like the rest of the world, is experiencing population aging, and this demographic transition will have a significant impact on age-related conditions such as dementia [1]. With nearly 7 million people affected [2], India has the fastest growing dementia rate worldwide and will soon host one of the largest populations of people with dementia. A large proportion of people with dementia are cared for by their immediate and extended families [3]. The role of family is paramount in dementia care in India and is rooted in the traditional concept of “seva,” which emphasizes service, honor, and respect for older people and a social expectation that they will be cared for by their children [4].

Despite affecting millions in India, the symptoms of dementia are often viewed as a normal part of aging, and there is a lack of awareness about the symptoms, treatment, and challenges associated with caring for a person with dementia [5]. Some family caregivers have no basic knowledge of dementia; many, despite receiving a dementia diagnosis, do not understand the implications of the diagnosis for themselves or their relatives with dementia [1,6]. Limited understanding can result in the person with dementia not receiving the necessary support and treatment to address their needs and improve their well-being, and it can also lead caregivers to feel publicly stigmatized, ashamed, or distressed [5]. Concomitant with a lack of care infrastructure and scarcity of resources, such as respite- and long-term care facilities, is the fact that family caregivers are often very isolated and without support [7]. In these circumstances, caregivers often experience increased burden, a decline in their mental and physical health, and a loss of income and productivity because of caregiving [8-11].

To ameliorate these burdens, greater focus on imparting knowledge and skills to empower caregivers for persons with dementia is crucial [5]. As many family caregivers enter their new role unprepared, they need information about what dementia care involves, care pathways, social and clinical care, sources of help, and other services available [12]. Provision of culturally salient dementia care resources, during diagnosis and postdiagnosis, may help caregivers gain perspective about their family member’s behaviors. Such resources would also help families understand dementia as a medical condition rather than attributing symptoms to moral deficits in the person themselves or in the care provided by their caregivers.

Technological innovations, especially digital media, can help improve dementia care. Digital media, particularly smartphones, can help caregivers access information online, monitor their own physiological and biometric data along with that of the person with dementia, and set reminders for medications and other therapies [13,14]. According to a report by the India Cellular & Electronics Association, nearly 830 million people in India are smartphone users, thus making smartphones and digital media crucial dissemination platforms for content creators and service providers [15].

In Australia, an innovative multimedia project called Moving Pictures is producing short films on dementia care, which are coproduced with people from culturally and linguistically diverse backgrounds [16]. The project is a collaboration between the National Ageing Research Institute (NARI) and Curtin University, and the films produced are based on the stories and lived experiences of family caregivers of people living with dementia as well as the expert views of key service providers. Taking into context the need for dementia care resources and the current technological uptake in India, authors from India, Australia, and UK have collaborated to develop Moving Pictures India to improve dementia care in India using digital media. The aim of Moving Pictures India is to coproduce 9 short films on common issues in dementia care with caregivers and stakeholders and to pilot the resources developed to determine whether the findings would support a large implementation trial. There are 4 main objectives of the study: (1) to video interview Indian caregivers and health professionals about cultural understandings of dementia, social and clinical care, sources of help, and care pathways; (2) coproduce 9 short films on dementia care with caregivers and stakeholders; (3) pilot the resources with caregivers to assess feasibility and acceptability using a randomized controlled trial (RCT) design; and (4) disseminate the films online for free and use analytics and qualitative feedback to develop an implementation trial. This paper describes the protocol of the study.

## Methods

### Methodological Approach

The methodological approach for the study follows the United Kingdom Medical Research Council guidelines for the development and evaluation of complex interventions [17]. The process of designing and evaluating complex health interventions includes development, feasibility and piloting, evaluation, reporting, and implementation. Mobilizing this methodology, this study uses robust mixed methods including video interviews, stakeholder consultation, community forums, a quasi-experimental trial, and big data analytics. Owing to its mixed methods design, this study is divided into 4 different phases based on the main objectives. The methods of each phase including the research design are described as follows.

#### Phase 1. Video Interviews: Intervention Development

In the first year of the study, video interviews with family caregivers and health professionals will be recorded to create the films for mobile devices targeting family caregivers and the Indian public. Family caregiver interviews will focus on initial perceptions of dementia symptoms, at what point medical intervention was sought and why, examples of successful collaboration between caregivers and services, and how the dementia care pathway unfolds for families. Health professional interviews will focus on working with doctors; going to the hospital; pain; eating, nutrition, and dental care; hygiene and incontinence; and later stages and palliative care. The topics for discussion in the interviews are based on patient and public involvement and clinician consultation. 

##### Inclusion Criteria

We will recruit family caregivers who are currently caring for a family member with dementia for at least 6 months. Health professionals include medical specialists (eg, geriatricians, old age psychiatrists), nurses, allied health care workers (eg, physiotherapists, social workers), or related professionals (eg, care coordinators, direct care workers) involved in providing health and community services to people living with dementia. We will include participants who speak either English, Hindi, or Kannada, have the capacity to consent, and are willing to participate in a video interview, snippets of which will be included in the final Moving Pictures India films and resources.

##### Recruitment and Sampling

The aim is to purposively recruit 25 family caregivers speaking either of the 3 aforementioned languages and representing different genders and socioeconomic classes, along with 25 health professionals who satisfy the inclusion criteria. The sample size was determined based on the research team’s extensive experience of sampling to ensure sufficient diversity. Participants will be invited to participate in a 30- to 60-minute video interview conducted in English, Hindi, or Kannada. Purposive and snowball sampling will be employed for recruitment. Data will be collected in Bengaluru, India.

Upon confirmation of interest, the researcher will forward a copy of the participant information and consent form (PICF) either by email or regular mail with a prepaid envelope. Contact will be made a few days later to gauge interest, answer any relevant questions, and arrange the interview. If the consent form is not received by the research team prior to the interview, it will be completed before starting the interview. All participants will be provided with a verbal overview of the study, time to read the PICF (if not done earlier), and an opportunity to seek clarification about any study-related matter from the researcher prior to the interview.

##### Data Analysis

Data will be translated, transcribed into English, and thematically analyzed [18-20] by the research team using NVivo version 12 or the latest version of the software. Deductive analysis will be used, informed by the cross-cultural care literature, and will focus specifically on how concepts such as aging (eg, “budhapan”), dementia (eg, “yadarsht khona” or losing memory), dementia symptoms (eg, “bak bak” or useless, repetitive talk), and care (eg, “seva”) are understood cross-culturally and in light of India’s rapid modernization and reduced availability of adult children to provide familial care. Digital resources will be cut from the recordings.

#### Phase 2. Coproduction of Films and Resources: Intervention Development

In the second year, the data from the first phase will be storyboarded to form the basis of 9 films and animations. The themes for the storyboards are based on common issues in dementia care arrived at through the researchers’ prior work [4,16] and will focus on the following themes: (1) signs of dementia; (2) care pathways; (3) self-help for caregivers; (4) recognizing and responding to unmet needs; (5) working with doctors and going to hospital; (6) pain; (7) eating, nutrition, and dental care; (8) hygiene and incontinence; and (9) later stages and palliative care. Storyboards will be internally reviewed for cultural appropriateness followed by realist and critical evaluation at a stakeholder workshop in Bengaluru using the nominal group technique. The nominal group technique is designed to democratically elicit ideas and is widely used in health and education research. It involves group members first working alone, then sharing ideas and undertaking group discussions, and finally, voting and ranking [21]. Stakeholders at the workshop will include the investigator team, film editor, dementia services, clinicians, researchers, and artists. Following stakeholder approval, the storyboards will be converted to Hindi/Kannada films (by the film editor) and animations (by the designer).

To evaluate the appropriateness of the films and animations, they will be member-checked with the original interview participants as well as with community members to ensure believability and trustworthiness [22]. Interview participants and community members will complete a survey (eg, whether expectations were met, level of enjoyment and interaction, key learnings, etc) in English, Hindi, and/or Kannada via telephone or online. Film and animation screenings with community members will be completed using a workshop format, and feedback will be used to improve the resources. A flowchart of this phase is illustrated in Figure 1.

**Figure 1 figure1:**
[figure not shown]
Study protocol flowchart of phase 2: Coproduction of films and resources. NIMHANS: National Institute of Mental Health and Neuro Sciences.

##### Inclusion Criteria

Members of stakeholder groups and the community members must be 18 years of age or over, have a smartphone, have the capacity to provide consent, and be literate in either English, Hindi, or Kannada.

##### Recruitment and Sampling

Family caregivers and health professionals who participated in phase 1 of the study will be asked to provide feedback on resources once they are completed. Community members (n=~300) speaking either of the 3 aforementioned languages, representing different genders and socioeconomic classes, and satisfying the inclusion criteria will be recruited in Bengaluru to test the films and resources. Bengaluru is one of the most multicultural and ethnically diverse cities in India and has a large migrant population due to its status as the information technology hub of the country [23,24]. Recruitment will be facilitated via invitations/advertisement (through email, hard copies, social media posts, newsletters, and public notices) to local senior citizens’ groups, social groups, Alzheimer’s and Related Disorders Society of India Bengaluru Chapter, community and health services, and institutes of higher education. Upon request, a member of the research team will give a talk about the study to groups of interested individuals. Participants will be invited to participate in one of 6-10 workshops (1-2 hours) in which films and resources will be screened and evaluated.

#### Phase 3. Pilot RCT: Intervention Assessment

To evaluate the impact of the resources produced, a pilot RCT will be conducted in the second and third year of the study (Figure 2). The pilot RCT will follow an experimental parallel group design with two arms aiming to assess the impact, feasibility, and acceptability of the resources of Moving Pictures India. The aims of the pilot RCT will be: (1) to test the feasibility of a full RCT with feasibility prespecified as >70% of participants expressing interest, consenting to participate, and >80% participation in follow up; (2) to test acceptability, prespecified as >70% of participants rating the intervention “very acceptable.”

**Figure 2 figure2:**
[figure not shown]
Study protocol flowchart of phase 3: pilot randomized controlled trial. NIMHANS: National Institute of Mental Health and Neuro Sciences; RCT: randomized controlled trial.

##### Inclusion and Exclusion Criteria

Participant inclusion criteria are aged 18 years and up, proficient in English and/or Hindi/Kannada, self-reported family caregiver of a person with dementia who has been involved in the caregiving process for at least 6 months, capacity to consent, and own a smartphone. Participants involved in the development phase will be excluded.

##### Recruitment and Sampling

Participants will be recruited in Bengaluru, India. Purposive and snowball sampling will be employed for recruitment. Family caregivers who accompany people with dementia to the Geriatric Clinic and Services Unit at the National Institute of Mental Health and Neuro Sciences (NIMHANS) will be recruited. Furthermore, advertisements will be posted in public spaces in the NIMHANS facility and distributed in hard or soft copy by the research team to relevant clients, through relevant NIMHANS services and other support and social groups. The materials will contain contact details for the NIMHANS-based research team (email/phone). Potential participants will be able to contact the research team to express their interest in the study. The researcher will describe the study procedures, and if the participant agrees to the study, the researcher will confirm the participant’s eligibility. Alternatively, if potential participants learn about the study from a NIMHANS service provider, the latter will provide the contact details of the research team or, with verbal consent from the interested individual, forward their details to the research team, who will make the initial contact to provide the necessary study information. Upon confirmation of interest, the researcher will forward a copy of the PICF either by email or regular mail with a prepaid envelope, or it can be obtained from the research team located at NIMHANS upon request. Contact through phone or email will be made a few days later to confirm interest, answer any questions, and arrange for a brief meeting to sign the consent form. Signed consent can also be provided by mail or electronically.

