##### Randomization and Blinding

Following consent, participants will be randomized into either an intervention arm that comprises usual clinical care plus access and use of the digital resources or a control arm comprising usual clinical care and access to nondementia resources (eg, a pamphlet on healthy living). Randomization will be done using computer-generated random number sequences, and the process will be overseen by a researcher not involved in the study. After allocation to groups, participants will be able to choose to receive specific instructions on how to access materials relevant to the condition (a brief instructional booklet) they have been allocated to either electronically, by regular mail, or in person. As a booster, participants in the intervention arm will also receive a monthly phone call from the research associate to help sustain intervention engagement over the long term, which is a risk to any digital trial [25]. Caregivers will not be told whether they are in the intervention or the control group to reduce potential bias. However, this blinding is not expected to be of any disadvantage, as all participants will have free and unlimited access to the Moving Pictures India materials after the pilot RCT.

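### Snowball recruitment, no one-caregiver-per-patient rule and individual randomisation allow linked caregivers to be split across arms, and control exposure to the films would go unmeasured

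*Protocol article*

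**What the plan says.** All of this is in the protocol article; no analysis plan is at hand.

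- **Recruitment and Sampling (Phase 3):** "Purposive and snowball sampling will be employed for recruitment". It takes place in one city, through one clinic, and by advertisements distributed "through relevant NIMHANS services and other support and social groups".
- **Inclusion and Exclusion Criteria (Phase 3):** an adult smartphone owner qualifies as a "self-reported family caregiver of a person with dementia who has been involved in the caregiving process for at least 6 months". The one exclusion listed is "Participants involved in the development phase will be excluded". The list does not limit enrolment to one caregiver per person with dementia.
- **Introduction:** "A large proportion of people with dementia are cared for by their immediate and extended families".
- **Randomization and Blinding:** "Following consent, participants will be randomized into either an intervention arm" with the digital resources, or a control arm with material unrelated to dementia. "Caregivers will not be told whether they are in the intervention or the control group to reduce potential bias". Everyone gets the films once the pilot is over. Only the intervention arm receives monthly calls.
- **Statistical Analysis:** 40 intervention and 20 control participants are expected. Scores are to be reported as differences between the randomised groups with 95% CIs.
- **Outcome Measures:** feasibility and acceptability are primary. Burden, mood and quality of life are secondary, measured at baseline, 3 and 6 months.

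The Limitations section does not mention contamination, and none of the feasibility criteria under Phase 3 measures control exposure.

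**The concern.** Snowball sampling brings in people who know each other. Support groups do the same, and the criteria as listed would let two relatives of one patient both enrol. Each is then randomised separately to material that one arm is meant not to see until the end. Two stated design choices thus pull against each other.

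If a control sees the films through a linked participant, the between-arm differences in the three secondary scales move toward zero. No item in the plan would show that this had happened, so a small difference could not be told apart from contamination. Whether controls can be kept unexposed under this recruitment also bears on whether a full randomised trial is feasible, which is the pilot's first aim. Later analysis cannot recover exposure that was not recorded during conduct.

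**Working it through.** **Inputs from the article:** 40 intervention and 20 control participants, so 2:1 allocation of individuals. The article gives no figure for linked participants, film sharing, effect size or intracluster correlation (ICC). Those below are assumptions.

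**1. Chance that a linked pair is split**
- Independent 2:1 allocation: 2 × (2/3) × (1/3) = 44.4%.
- Fixed totals: 2 × 40 × 20 / (60 × 59) = 45.2%.
- So about 55% of pairs would share an arm.
- At least one split pair among k pairs: 1 − (5/9)^k, which is 44% for k = 1, 83% for k = 3 and 95% for k = 5.

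**2. Chance that a linked control has a film-arm partner**
- In a pair: 2/3 = 67% (40/59 = 68% with fixed totals).
- In a chain of three: 1 − (1/3)² = 89%.

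**3. Illustrative dilution of the secondary differences**

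Controls with a film-arm partner = share in pairs × 2/3 × 20. Shrinkage = share in pairs × 2/3 × sharing rate, if sharing carries the full effect.

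| Assumed share in pairs | Controls with film-arm partner | Shrinkage, half share | Shrinkage, all share |
|---|---|---|---|
| 20% | 2.7 | 7% | 13% |
| 40% | 5.3 | 13% | 27% |
| 60% | 8.0 | 20% | 40% |

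For scale, the standard error of a between-arm difference in SD units is √(1/20 + 1/40) = 0.274, so the 95% half-width is 1.96 × 0.274 = 0.54 SD. With an assumed true difference of 0.5 SD, 20% shrinkage moves the estimate by 0.10 SD, well inside that interval.

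**4. Independence**

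Take 40% of 60 in pairs (12 pairs) and an assumed ICC of 0.3.
- *Between-arm difference, individuals randomised:* the variance factor is 1 minus the mean pairwise correlation. That correlation is 12 × 0.3 / (60 × 59 / 2) = 3.6/1770 = 0.002, so the factor is 0.998. Split pairs offset same-arm pairs.
- *Acceptability, n = 40 at 70%:* the simple half-width is 1.96 × √(0.21/40) = 14.2 points. With individual randomisation the design effect is 1 + 0.4 × (2/3) × 0.3 = 1.08, giving 14.2 × √1.08 = 14.8 points. If linked people were allocated together it would be 1 + 0.4 × 0.3 = 1.12, giving 15.0 points.

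**The case against.** The case against has real force, and most of it limits the point rather than removing it.

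- **Linked enrolment and sharing are not stated.** A reader might infer that linked caregivers, even two for one patient, *will* be enrolled and will forward films. The article says neither. Clinic attendance, advertisements and provider referral also supply participants, and how access is controlled during the trial is not described. What stands is that the stated rules permit it and no safeguard is described.
- **The shrinkage is conditional and generous.** A forwarded film does not bring the booklet or monthly calls, so assuming full transfer of effect overstates the dilution at any given sharing rate.
- **Primary results are not diluted.** Acceptability is rated by people using the intervention, and progression rests on that rating. The parameters that the article singles out for the next trial are uptake and completion, not score differences. This is correct and keeps the point modest.
- **Blinding.** A reader might infer that linkage undoes the blinding. Visibly different content and calls to one arm already weaken it; linkage only adds to that.
- **Independence.** A reader might infer that linkage invalidates the standard errors. Under individual randomisation the between-arm variance is essentially unchanged (factor 0.998 above), and the acceptability interval widens by about half a point.
- **A condensed article.** The full protocol may hold a one-per-patient rule or an exposure question. If so, that part falls away. The combination of recruitment and randomisation is nevertheless stated here.

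**Conclusion.** The point holds as a modest design weakness with a nearly free remedy. As listed, the rules let linked caregivers, including two relatives of one patient, fall into opposite arms in about 44-45% of linked pairs. That figure follows from the 40:20 allocation alone. The consequence is dilution, of unknown size, of the secondary differences in burden, mood and quality of life. The illustrative 7-20% rests on three assumptions that the article does not supply: 20-60% of participants in pairs, half of the film-arm partners sharing, and full transfer of effect. The primary acceptability rating is not diluted, and the documents do not support a claim that blinding or independence fails because of linkage. The main loss is that the pilot would not learn whether its control arm stayed unexposed.

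**What to change.** Keep snowball recruitment and individual randomisation, and make two changes:

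1. In the Phase 3 inclusion criteria, state that only one caregiver per person with dementia is enrolled. This takes the chance of splitting a same-patient pair from 44-45% to zero.
2. At the existing 3- and 6-month assessments, ask whether the participant has seen any Moving Pictures India film, and report control-arm exposure as a feasibility outcome with a 95% CI. This covers links through friends and groups, which the first change does not. With 20 controls the answer will be coarse: if none reports exposure, the exact upper limit is 1 − 0.025^(1/20) = 17%.

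Recording who referred whom, for description only, is optional.

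Do not place later referrals in their referrer's arm. Recruits arrive over several months, so their allocation would be known before consent to anyone who knew the referrer's arm. It would also slightly widen the acceptability interval (14.8 to 15.0 points in the example above).

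**Cost:** a few second caregivers from the same family are not enrolled, and there is one extra question at each follow-up. Naming the films may hint at allocation, so put the question after the outcome scales.
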